### Management of the visits

Based on the test’s reported 90% specificity and 41% sensitivity we anticipate that 520–550 participants in the intervention arm will have a positive test result. These will be offered a chest X-ray in accordance with local requirements for prioritisation and will be referred for a non-contrast thoracic CT scan. If there is a suspicious opacity on the chest X-ray or initial CT scan a contrast enhanced staging CT will be undertaken. As a quality control measure no participant undergoing CT screening in the test positive arm will have all their 5 CTs reported by same radiologist. Nodule size will be currently reported as the mean of 2 diameters at 90° angles, volumetric analysis is starting soon on both sites with diameter and volume to be reported. If the initial CT scan reveals no evidence of lung cancer then subsequent CT scans will be offered 6 monthly for 24 months. An appointment window of ± 4 weeks will be initiated for each scheduled CT scan.

If a test positive participant has had a chest X-ray in the previous 1 month, or a CT scan in the previous 3 months, these can be reviewed as part of the study. With the participant’s consent chest X-rays or CT scans prior to study entry will be retrospectively coded. The participant will proceed to have the series of up to 5 CTs.

Participants will receive appointments via post/email, according to patient preference. Participants will be called 2–4 days before each CT scan appointment. Individuals with abnormalities as classified by the radiology/respiratory physician’s study panel on baseline CT scan or subsequent CT scan will be followed up over the study period or referred for NHS clinical care as appropriate. All individuals entering the study will be flagged and followed-up via the Scottish Cancer Registry in the Electronic Data Research and Innovation Service (eDRIS) [26]. Participants who develop lung cancer will be followed-up via their medical records to assess both time to diagnosis and stage of disease at diagnosis. If no histological stage is available, stage will be assessed by a panel of three respiratory physicians blind to allocation status of the study subjects from chest X-rays or CT, or if no imaging is available, medical assessment of stage will be carried out.

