### Outcomes

#### Primary

The difference, at 24 months after randomisation, between the rates of patients with stage III, IV or unclassified lung cancer at diagnosis in the intervention arm, and those in the control arm;

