#### Secondary

numbers at 24 months after randomisation, in the different stages at diagnosis (III/IV/U/other) in the intervention arm and the control arm;difference, after 24 months, between costs and outcomes between the intervention arm and in the control arm and cost-effectiveness of the test compared to standard practice;differences, after 24 months, of lung cancer mortality, all-cause mortality and cancer-specific mortality rates between the intervention arm and in the control arm;differences, after 5 and 10 years, of long-term future mortality rates in the intervention arm and in the control arm;differences, after 24 months in (i) the number of patients with stage III, IV or unclassified lung cancer at diagnosis in the test-positive group and those in the test-negative group and (ii) stage at diagnosis in the test-positive and test-negative group;difference between the test-positive, test-negative groups and the control arm at 1, 3, 6, and 12 months in scores for EQ5D [29], Positive and Negative Affect Schedule [30], revised Illness Perception Questionnaire adapted to refer to lung cancer and lung cancer risk [31], Lung cancer risk perception, Health anxiety subscale of Health Orientation Scale [32], the Adapted Lung Cancer Worry Scale [33] and Impact of Events Scale [34] (for the test-positive group, the test-negative group only) and differences in smoking behaviour and health service use. Long-term scores for the same outcomes for the test-positive group at 18 and 24 months;difference in incidence at 24 months, and after 5 and 10 years, in other clinical measures such as Cerebrovascular disease, Chronic Obstructive Pulmonary Disease, hospital stays, and outcomes identified through the Scottish Morbidity Record (SMR) linkage in the intervention arm and in the control armnumbers in all groups at 24 months (test-positive, test-negative and control) undertaking subsequent investigations such as chest X-ray, CT and bronchoscopy (Table 1)

**Table 1 Tab1:** Data Collection Timeline

Assessment/Procedures	Timeline (± 2 weeks)				
	Visit 1 (~30-45mins)		Visit 2 (~30mns)	➢ *EarlyCDT Positive Test Participants may visit or call.* ➢ *EARLY CDT Negative Test Participants may attend for further information/advice only.*	
*Informed Consent*	X				
*Inclusion/Exclusion Criteria*	X				
• *Review/Record only Relevant Medical History relating to IC/EC*	X				
• *Review/Record Relevant Medications* • *Relating to IC/EC*	X				
*Blood Sample*	X				

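### Every named stage outcome stops at 24 months, when the last screening CT is due; late-stage and total lung cancer incidence after that is not defined, although the stated power relies on later events

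*Protocol article*

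**What the plan says.** All references are to the Protocol article.

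- **Outcomes, Primary:** "The difference, at 24 months after randomisation, between the rates of patients with stage III, IV or unclassified lung cancer at diagnosis", compared between the arms.
- **Outcomes, Secondary, stage:** "numbers at 24 months after randomisation, in the different stages at diagnosis (III/IV/U/other) in the intervention arm and the control arm". The comparison of stage between test-positive and test-negative participants is also placed at 24 months.
- **Outcomes, Secondary, long term:** one item is "differences, after 5 and 10 years, of long-term future mortality rates in the intervention arm and in the control arm". Another is "difference in incidence at 24 months, and after 5 and 10 years, in other clinical measures", for which vascular, respiratory and admission outcomes serve as examples. That item also has an open category, worded as "outcomes identified through the Scottish Morbidity Record (SMR) linkage". Lung cancer stage and lung cancer incidence are not named at 5 or 10 years.
- **Management of the visits:** for test-positive participants with a clear first scan, "subsequent CT scans will be offered 6 monthly for 24 months". Table 1 shows CTs at 0, 6, 12, 18 and 24 months. The same section says "All individuals entering the study will be flagged and followed-up via the Scottish Cancer Registry", with no end date.
- **Sample size calculations, Main study:** the revised design has 12,000 participants, a late-stage rate of 600/100,000 per year and 80% power for a 35% reduction. That power depends on recruitment spread over 2 years and on analysis once everyone has at least 2 years of follow-up. Longer recruitment is said to raise it to 83%. A 3-year endpoint is mentioned only as a route to power above 90%.
- **Proposed analyses:** a Cox model with censoring at loss to follow-up. No administrative cut at 24 months is stated.

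**The concern.** A screening programme lowers late-stage incidence by finding, while still early, cancers that would later have presented late. The gain is visible only once the matching control cancers have surfaced. With scans running up to the reading date, an early cancer found at month 18 or 24 has had almost no time to produce a late-stage counterpart in the control arm. Conversely, a late-stage cancer that a scan brings forward from after month 24 is counted, but only in the intervention arm. Both effects work against the intervention at 24 months.

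Three things are at stake:

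- Late-stage cases averted by the later scans may never be counted in a prespecified outcome.
- Screening is expected to produce an excess of total cancers at 24 months. Lead time fades with further follow-up and overdiagnosis does not, so one reading at the end of screening cannot separate them.
- The sample size leans on events after 24 months, yet no outcome that includes them is defined.

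**Working it through.** **1. The plan's own power figure.** Inputs from the sample size section: 6,000 per arm, control rate 0.006 per year, hazard ratio 0.65 (intervention rate 0.0039), two-sided 5%.

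Expected events = 6,000 × mean over follow-up t of [(1 − e^(−0.006t)) + (1 − e^(−0.0039t))].

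Power = Φ(√(D/4) × |ln 0.65| − 1.96) by Schoenfeld, or Φ(√D × 0.35/1.65 − 1.96) by Freedman, where D is the number of events.

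| Follow-up counted | Events | Power (Freedman–Schoenfeld) | Protocol states |
|---|---|---|---|
| 2–4 years (2-year accrual, minimum 2) | 177 | 80.5–81.7% | 80% |
| 2–4.5 years (2.5-year accrual) | 191 | 83.5–84.6% | 83% |
| 3–5 years (2-year accrual, minimum 3) | 235 | 90.2–91.0% | above 90% |
| Exactly 36 months | 177 | 80.5–81.7% | – |
| Exactly 24 months | 118 | 63.5–64.9% | – |

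For the last row: 6,000 × (0.01193 + 0.00777) = 118. Schoenfeld: √29.5 × 0.4308 − 1.96 = 0.38, so 64.9%. Freedman: 10.87 × 0.2121 − 1.96 = 0.35, so 63.5%. All three stated figures reproduce only when events beyond the nominal time point count. With a strict 24-month cut, 80% power would need about 17,444 participants.

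**2. Share of control counterparts surfaced by 24 months.** Assume an exponential lag from early detectability to late-stage diagnosis with mean L years, perfect scans at 0, 0.5, 1, 1.5 and 2 years, and a constant onset rate. Per unit onset rate, the first scan finds L cancers and each later scan finds d = L(1 − e^(−0.5/L)). A cancer found at time t would have surfaced by 24 months with probability 1 − e^(−(2−t)/L).

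For L = 2: found = 2 + 4 × 0.442 = 3.77. Surfaced = 2 × 0.632 + 0.442 × (0.528 + 0.393 + 0.221 + 0) = 1.77. Share = 47%.

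The protocol gives no lag. Crude prevalence/incidence ratios from its figures are 2%/1% per year = 2 years (entry risk), 2%/0.68% = 2.9 years (revised total rate) and 2%/0.4% = 5 years (reference screening study). They mix stages and settings and are only a guide.

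| Mean lag L | First-scan cancers, by 24 months | All scans, by 24 months | All scans, by 5 years |
|---|---|---|---|
| 1 y | 86% | 61% | 98% |
| 2 y | 63% | 47% | 88% |
| 3 y | 49% | 38% | 77% |
| 5 y | 33% | 28% | 60% |

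**3. Fuller natural-history simulation.** Protocol inputs: 600/100,000 late-stage per year, 80% late, 41% of prevalent cancers test-positive, CT sensitivity 67%, five 6-monthly CTs. Assumed: early preclinical phase with mean 1–3 years, late preclinical phase 0.25–1 year, 10–41% positivity for cancers starting after the test, first CT at 1–2 months, no overdiagnosis. This gives 36 settings. Control late-stage cases per 6,000 are 36 per year: 72, 108 and 180 at 24 months, 36 months and 5 years.

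| | 24 months | 36 months | 5 years |
|---|---|---|---|
| Late-stage cases averted per 6,000 | 3–18 | 9–31 | 14–47 |
| Rate ratio (1 − averted/control) | 0.75–0.96 | 0.71–0.92 | 0.74–0.92 |

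Repeat runs differ by about 0.01 in the ratio. The 24-month count is roughly 10–65% of the 5-year count (median 38%). Setting by setting, the median change in the rate ratio from 24 months is about −0.04 at 36 months and −0.01 at 5 years. Total cancers, intervention over control, have a median of about 1.3–1.4 at 24 months and 1.03 at 5 years, although the model contains no overdiagnosis.

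**The case against.** A reader might infer that most of the averted late-stage cases are still invisible at 24 months, and that a real stage shift would therefore look null. The documents do not support that.

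- They give no progression time. Over all five scans, fewer than half of the counterparts have surfaced only if the mean lag exceeds about 1.5–2 years; for first-scan cancers it must be nearly 3 years. In about six of the 36 simulated settings, at least half of the 5-year benefit is already visible.
- Twenty-four months is 40% of 5 years, so a constant ratio would by itself put 40% of the 5-year count at 24 months. The median of 38% is close to that, in line with the small change in the ratio. Later follow-up mainly adds events and precision.

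Two further points have force. Later data are unnamed, not excluded: registry flagging has no end date, the long-term list is open-ended, and a full protocol or analysis plan may say more. Nor is it established that stage will be read strictly at 24 months, since the power text counts later events and the Cox paragraph states no cut. Randomised mortality at 5 and 10 years, which lead time does not bias, is already planned.

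What stands is that the article lists its outcomes with time points and leaves out the trial's own disease endpoint after 24 months. An open category does not prespecify it, and the power basis makes the gap more visible.

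**Conclusion.** The point holds in a limited form. All named stage outcomes end at 24 months, when the last CT is due, and no later outcome covers lung cancer stage or incidence. The consequences differ in firmness:

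- **Firm:** the 80% power needs events beyond 24 months. Read as the primary outcome is worded, power is about 64%. The two passages must be reconciled.
- **Firm in direction, uncertain in size:** some averted late-stage cases fall after the reading. The share captured by 24 months is roughly 10–65% of the 5-year count, resting wholly on assumed phase lengths and test positivity. The effect on the rate ratio is modest.
- **Firm in logic:** a 24-month excess of total cancers cannot be divided between lead time and overdiagnosis. In a model without overdiagnosis the excess shrinks from about 30–40% to about 3% by 5 years (medians).

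This is a cheap improvement to the outcome list. It is no reason to move the primary endpoint or to discount a 24-month result.

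**What to change.** 1. Keep the 24-month primary outcome.
2. Add as secondary outcomes the rate of stage III, IV or unclassified lung cancer and the rate of all lung cancer, by arm and per randomised participant, at the planned 5- and 10-year linkages and, if an extract is feasible, at 36 months. Use the same adjusted Cox model.
3. State whether the primary Cox analysis censors at 24 months or uses all follow-up to the analysis date, and align the outcome wording and the power statement with that choice.
4. Note, whichever way the result falls, that the 24-month stage comparison is interim with respect to lead time. Do not add a rule that applies only to a null result.

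**Cost:** a few lines in the outcome list and one extra extract for 36 months, with no added participants or visits. Later cases would need staging from registry data, or by the blinded panel where no histological stage exists. Timing is a limit. With 8,639 recruited by March 2015 after about 18 months (roughly 480 a month), the remaining 3,361 take about 7 more months, to around autumn 2015. The last recruits then reach 36 months in autumn 2018, after the stated end date of 31/07/18. The End of study section defines the end differently, from the last test-related scan plus 24 months, so the governing date should be stated as well.

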#### Secondary

numbers at 24 months after randomisation, in the different stages at diagnosis (III/IV/U/other) in the intervention arm and the control arm;difference, after 24 months, between costs and outcomes between the intervention arm and in the control arm and cost-effectiveness of the test compared to standard practice;differences, after 24 months, of lung cancer mortality, all-cause mortality and cancer-specific mortality rates between the intervention arm and in the control arm;differences, after 5 and 10 years, of long-term future mortality rates in the intervention arm and in the control arm;differences, after 24 months in (i) the number of patients with stage III, IV or unclassified lung cancer at diagnosis in the test-positive group and those in the test-negative group and (ii) stage at diagnosis in the test-positive and test-negative group;difference between the test-positive, test-negative groups and the control arm at 1, 3, 6, and 12 months in scores for EQ5D [29], Positive and Negative Affect Schedule [30], revised Illness Perception Questionnaire adapted to refer to lung cancer and lung cancer risk [31], Lung cancer risk perception, Health anxiety subscale of Health Orientation Scale [32], the Adapted Lung Cancer Worry Scale [33] and Impact of Events Scale [34] (for the test-positive group, the test-negative group only) and differences in smoking behaviour and health service use. Long-term scores for the same outcomes for the test-positive group at 18 and 24 months;difference in incidence at 24 months, and after 5 and 10 years, in other clinical measures such as Cerebrovascular disease, Chronic Obstructive Pulmonary Disease, hospital stays, and outcomes identified through the Scottish Morbidity Record (SMR) linkage in the intervention arm and in the control armnumbers in all groups at 24 months (test-positive, test-negative and control) undertaking subsequent investigations such as chest X-ray, CT and bronchoscopy (Table 1)

**Table 1 Tab1:** Data Collection Timeline

Assessment/Procedures	Timeline (± 2 weeks)				
	Visit 1 (~30-45mins)		Visit 2 (~30mns)	➢ *EarlyCDT Positive Test Participants may visit or call.* ➢ *EARLY CDT Negative Test Participants may attend for further information/advice only.*	
*Informed Consent*	X				
*Inclusion/Exclusion Criteria*	X				
• *Review/Record only Relevant Medical History relating to IC/EC*	X				
• *Review/Record Relevant Medications* • *Relating to IC/EC*	X				
*Blood Sample*	X				
*Baseline Questionnaire*	X				
*Thank you letter to Control Group*		X			
*EarlyCDT- Lung Test Result Letter*		X			
*GP Results Letter & ICF copy (negative)*		X			
*Result Discussion/ Imaging Schedule*			X		
*Provide PIS 2*			X		
*GP Result Letter & ICF copy (positive)*			X		
EarlyCDT – Lung Test Positive Result Participants – Imaging Schedule					
	Timeline(± 12 weeks)				
	0	6 months	12 months	18 months	24 months
*CXR*	X				
*CT Scan*	X	X	X	X	X
*Scheduled every 6 months, if participant enters NHS clinical care pathway, subsequent study CT scans will be cancelled.*		*Research team member will call 2–4 days before each scheduled CT scan to check health status and attendance.*			

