### AIMS

To assess the effectiveness of the test in increasing early stage lung cancer detection, thereby reducing the rate of late stage (III/IV/U) presentation compared to standard practice; to assess the cost-effectiveness of the test compared to standard practice; to assess the impact of the test on quality of life, positive and negative affect, illness perceptions, lung cancer risk perception, health anxiety, lung cancer worry, subjective stress related to screening, smoking behaviour and health service use.

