### Proposed analyses

Characteristics of participants will be compared informally between treatment arms at baseline. The main analysis of the primary outcome will be intention-to-treat. Cox proportional hazards models which will be used to estimate the hazard ratio of the rate of late stage lung cancer in the intervention arm compared to the control arm. Participants who are lost to follow up will be censored. The models will adjust for age, gender smoking history, socioeconomic status and practice. If appropriate, random cluster effects will be included rather than fixed effects for practices. A similar methodology will be used for the secondary outcomes of comparisons of mortality rates. A subsequent analysis will compare the outcomes of those with a positive test in comparison to those in the intervention group with a negative test (primary contrast for this analysis) and those in the control group. Comparisons of proportions will be carried out using chi square tests. Fisher’s exact test will be used if the number of events is small.

Psychological and behavioral outcomes will be compared between the three groups (Test-positive, Test-negative and the control group) at baseline using analysis of variance (or non-parametric tests if there is evidence of non-normal distribution of scores) for continuous measures and *χ*
^2^ tests for categorical measures. Psychological (HADS Score) and behavioral measures will be described at each follow up time point and multilevel regression models will be used for analyses to take account of repeated measurements during follow up [38].

Poisson regression models, adjusting for follow up time if necessary, will be used to investigate the other clinical measures (secondary outcomes 7 and 8).

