### Cost effectiveness analysis

A short-term within-trial analysis will compare the costs and outcomes associated with the intervention arm to those of the comparison arm at 24 months, with a focus on cost-per-case detected. A longer term analysis will employ a decision analytic model to link the short term outcomes measured within the trial to potential longer term impacts on health, in terms of impacts on morbidity and mortality of early detection and treatment, to allow the estimation of cost-per Quality Adjusted Life Years gained. Both analyses will take the perspective of the NHS and personal social services and conform to the reference case favoured by NICE [39].

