### Data collection & management

#### Data collection

All research blood samples will be transported to the University of Nottingham for processing, and then transported to the US for Test processing by Oncimmune. All samples will be stored under custodianship as per UK Biobank guidelines [40]. Sample Analysis and Chain of Custody Plans are documented in the Study Operations Manual. The participant’s medical notes (GP and hospital) paper or electronic will act as source data for relevant past medical history, subsequent medical conditions, hospital admissions and diagnostic reports.

Psychological and behavioural data will be collected on the first 10,000 participants through a baseline questionnaire administered during Visit 1. Follow-up data will be collected between 1 and 12 months on subsets of the intervention and control arms and at 18 and 24 months for the EarlyCDT®-Lung Test-positive group. Data collected at baseline will include the EQ5D, Hospital Anxiety and Depression Scale, Positive and Negative Affect Schedule, revised Illness Perception Questionnaire adapted to refer to lung cancer and lung cancer risk, lung cancer risk perception, items from the Health Orientation Scale, the adapted Lung Cancer Worry Scale, smoking behaviour and demographic details. Follow-up questionnaires include the same measures, plus health service use and Impact of Events Scale and health service use for those who had the test. The Hospital Anxiety and Depression Scale is not included in follow-up questionnaires and the EQ-5D is not included in the 3 months follow-up questionnaire.

All participants in the positive group will be approached with the recruitment aim of 300 from this group. The TCTU will use an electronic randomisation tool to randomly sample patients from the test-negative group and control arm, stratified by the two study centres. Twenty-one individuals will be sampled each week and invited to complete follow-up questionnaires with an aim of recruiting 300 from both groups (based on an anticipated response rate of 67%).

Participants who receive a diagnosis of lung cancer will not be followed up subsequent to receiving the diagnosis.

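### For the questionnaire outcomes the article sets only contrasts of test-result groups with control, so the impact of the test itself, which is the stated aim, has no randomised estimate

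*Protocol article*

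**What the plan says.** The Aims section of the Protocol article sets out "to assess the impact of the test on quality of life, positive and negative affect, illness perceptions, lung cancer risk perception" and further psychological measures, ending with "smoking behaviour and health service use". The subject of the aim is the test, not a particular result.

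The secondary outcome that answers this aim is the "difference between the test-positive, test-negative groups and the control arm at 1, 3, 6, and 12 months in scores for EQ5D" and on the other scales, smoking and service use. The Impact of Events Scale is restricted there to the two tested groups. The substudy sample size uses the same contrasts, with each test group set against the control arm.

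Proposed analyses adds that "Psychological and behavioral outcomes will be compared between the three groups (Test-positive, Test-negative and the control group) at baseline". That sentence concerns baseline only. For follow-up the section names multilevel models for repeated measures but fixes no contrast.

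On sampling, Data collection states: "All participants in the positive group will be approached with the recruitment aim of 300 from this group". Test-negatives and controls are randomly sampled within the two centres, with an aim of 300 each.

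Other outcomes are compared by randomised arm. Under Secondary outcomes these include mortality, hospital stays and outcomes from morbidity-record linkage. For costs, "A short-term within-trial analysis will compare the costs and outcomes associated with the intervention arm to those of the comparison arm at 24 months".

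**The concern.** Randomisation supports one comparison, everyone offered the test against everyone not offered it. Test-positive and test-negative groups form only after randomisation. The test is meant to sort people by lung cancer risk, so setting test-positives against an unselected control arm mixes the effect of a positive result with the kind of person who tests positive.

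The net effect matters here. The Discussion expects effects that may run in opposite directions: a negative result might reinforce smoking and a positive one might reduce it. A decision about a screening service needs the balance of the two across the whole arm, and no stated questionnaire analysis gives it.

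The sampling adds a practical risk. Anyone who later forms an intervention-arm mean by pooling the two tested samples gives test-positives half the weight, although they make up about a tenth of the arm.

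**Working it through.** **Inputs**
- 200 analysable (300 recruited) per group, SD 15.04, differences of 4.2 between groups and 3.00 within a group, smoking 80% against 67%, 80% power, two-sided 5% (Sample size calculations, Substudies).
- 520 to 550 test-positives expected in the intervention arm, from 90% specificity and 41% sensitivity (Management of the visits).
- Arm size of 5,000 before the sample size increase, or 6,000 for the current total of 12,000. The allocation ratio is not stated; 1:1 is assumed.

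**Step 1: the plan's own figure.**
- Between groups: n = 2 × (1.960 + 0.842)² × 15.04² / 4.2² = 202 per group (power 79.7% at 200).
- Within a group: (2.802 × 15.04 / 3.00)² = 198.
- Smoking: 180 per group, or 195 with continuity correction.

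The stated 200 per group is reproduced.

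**Step 2: shares.**
- Sample: 300 / (300 + 300) = 50% test-positive.
- Arm of 5,000: 520/5,000 = 10.4% to 550/5,000 = 11.0%.
- Arm of 6,000 with the stated counts: 520/6,000 = 8.7% to 550/6,000 = 9.2%.
- Arm of 6,000 with the counts rescaled: 6,000 × (0.41p + 0.10(1 − p)) gives about 619 to 674 positives, or 10.3 to 11.2%, for an assumed prevalence p of 1 to 4%.

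On the stated counts, over-representation runs from 0.50/0.110 = 4.5-fold to 0.50/0.087 = 5.8-fold.

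**Step 3: what unweighted pooling would do, if anyone did it.** Let D be the test-positive minus test-negative difference. The error in the arm mean is (0.50 − w)D. At w = 0.104 this is 0.396D.
- Suppose smoking falls 13 points in test-positives and test-negatives match controls. The pooled sample shows 0.50 × 13 = 6.5 points. The arm effect is 0.104 × 13 = 1.35 points.
- Suppose, on a scale with SD 15.04, test-positives shift by +4.2 and test-negatives by −1. The pooled sample shows 0.5 × 4.2 − 0.5 × 1 = +1.6. The arm effect is 0.104 × 4.2 − 0.896 × 1 = −0.46, with the opposite sign.

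**Step 4: precision of the weighted contrast.** The standard error in SD units is √[(w² + (1 − w)²)/n + 1/n].
- Weighted, w = 0.104, n = 200: √[(0.0108 + 0.8028 + 1)/200] = 0.0952. Detectable difference 2.80 × 0.0952 = 0.267 SD. Over w = 0.087 to 0.110 it is 0.269 to 0.266 SD.
- Planned two-group contrast: 2.80 × √(2/200) = 0.280 SD.

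The SD-unit result does not depend on the scale. That matters because the 4.2 points belong to the Impact of Events Scale, for which the outcome list gives no control data.

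**Step 5: dilution.** If only test-positives change, they must shift by 0.267/0.104 = 2.6 SD for the arm contrast to reach its detectable size. For smoking at 80% (SD 0.40), 0.267 SD is about 0.107, or 11 percentage points.

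**The case against.** The best defence is that comparison by result is a deliberate question. The Abstract promises to assess harms from false results and benefits of true negatives, and the Discussion asks how a positive or negative result affects behaviour. The substudy is powered for those contrasts, and each includes the randomised control arm. This stands: the three-group analysis is legitimate and should stay, and there is no basis for insisting that the arm contrast displace it as the leading result. It does not supply an answer to the aim on the impact of the test.

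A second defence is that weighting, or an arm contrast, could sit in an analysis plan that is not shown. This stands in part. The outcome definition and the power calculation do fix the contrasts, however, and elsewhere the article puts the arm comparison first and treats comparison by test result as a subsequent analysis.

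Four stronger readings are tempting, but the documents do not support them:
- **No service-use outcome is compared by arm.** Hospital stays, linked outcomes and costs are.
- **The plan contains a biased pooled mean.** No unweighted pooled mean is proposed. Test-negatives are randomly sampled and the arm shares will be known.
- **The economic analysis rests on this sample.** Its data source is not stated. The within-trial focus is cost per case detected, and the 18- and 24-month questionnaires go only to test-positives.
- **An arm contrast is possible for every scale.** The Impact of Events Scale has no control data.

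**Conclusion.** The point holds for the questionnaire outcomes collected in all three groups up to 12 months: EQ-5D, the psychological scales other than the Impact of Events Scale, smoking behaviour and self-reported service use. For these the stated aim is the impact of the test, but the stated contrasts are by test result against control, and no analysis is named that estimates the randomised effect.

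The sample is 50% test-positive against roughly 9 to 11% in the arm, so any arm-level figure from it needs weights. This is a risk to prevent, not an error already in the plan. The weighted contrast is feasible at about 0.27 SD with 200 per group, slightly better than each planned contrast.

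The conclusion assumes 1:1 allocation, the stated 520 to 550 positives or their rescaling, equal SDs and 200 analysable per group. It also assumes that controls are asked about service use. The secondary outcome implies this, but the wording in Data collection is unclear. These are secondary outcomes, and the primary comparison is untouched.

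**What to change.** - Add an intervention-versus-control contrast for the outcomes named above: (share positive × test-positive mean + share negative × test-negative mean) − control mean. Use the observed shares of the intervention arm (about 0.10 and 0.90) and design-based standard errors that respect the sampling by centre. EQ-5D is not in the 3-month questionnaire, so its contrast applies at 1, 6 and 12 months.
- Keep the three-group results, labelled as contrasts by a result that follows randomisation.
- Use the same weights for any arm-level EQ-5D or service-use mean drawn from this sample.
- State that a null arm contrast is not evidence of no effect in test-positives, given the dilution.

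The cost is one extra analysis with a weighting step, and no new data up to 12 months. It cannot provide an arm-level EQ-5D at 24 months, because only test-positives are followed that far. Nor does weighting to arm shares remove non-response bias: the anticipated response rate is 67%, so responders should be compared with non-responders in each group.
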